#### 11.4.4. Relationship between adverse events and vaccine

Investigators should have measures to determine the causality of all AE and abnormal laboratory indicators to vaccination promptly, to identify SAEs and groups, convergent AE related to vaccination during clinical studies, and to suspend and terminate clinical studies on time to minimize harm to participants. Whether the adverse event is related to vaccination and the degree of correlation shall be determined according to the following principles.

**Not related:** the participant did not use the investigational vaccine, the AE occurred in an illogical chronological sequence with the administration of the investigational vaccine, or other significant causes could have led to the AE.

**Unlikely related:** evidence of investigational vaccination; AE more likely to be due to other causes; repeat investigational vaccination negative or inconclusive

**Possibly related:** evidence of investigational vaccination; temporal sequence of AE to investigational vaccination is reasonable; AE cannot be ruled out as being caused by

---

the investigational vaccine but may also be due to other causes.

**Probably related:** evidence of investigational vaccination; the chronology of AE with investigational vaccination is reasonable; AE is more plausibly explained by investigational vaccine than other causes.

**Related:** evidence of vaccination with the investigational vaccine; the temporal sequence of the AE with the administration of the investigational vaccine is reasonable; the AE is more plausibly explained by the investigational vaccine than by other causes; repeated positive vaccination with the investigational vaccine; the AE profile is consistent with previous knowledge of this or this type of vaccine.

Of these, "definitely related", "probably related", and "possibly related" were classified as "vaccine-related". "Unlikely related" and "Not related" are classified as "not vaccine-related"

#### **11.4.5. Outcome of AE**

Outcome of AEs included: Recovered, Recovering, Unchanged, Recovered with sequelae, and Other (Death, Unknown).

#### **11.5. Immunogenicity observation method**

Participants in the immunity subgroup: about 5.0 mL of venous blood will be collected and placed in a procoagulant tube (containing only procoagulant) before vaccination, 7 days, 14 days, 28 days, 3 months, and 6 months after vaccination for detection of live virus neutralizing antibody and specific IgG antibody of current epidemic strain.

Participants in the immunity subgroup: An additional 15mL venous blood will be

---

collected before vaccination, 7 days, 14 days, 28 days, and 3 months after vaccination to detect IL-2, IL-4, IL-13, and IFN- $\gamma$  cytokine levels (ELISpot method).

## **11.6. Biospecimen management**

### **11.6.1. Handling, storage, and transportation of blood samples**

Blood samples for humoral immunoassays: Venous blood is collected and waited for adequate clotting, then centrifuged to separate the serum within 4 hours. If the blood sample cannot be centrifuged on the same day, it needs to be stored in a refrigerator at 2~8°C and the storage temperature needs to be recorded. The serums to be tested and the backup serums should be locked, managed by special personnel, and temperature recorded according to SOP requirements, stored at -20 ° C or below. The transport temperature should be kept below -20 ° C. The cold chain was abnormal when the temperature of serum was > -20°C and < 0°C during storage and transportation, and broken when the temperature was  $\geq 0$  °C.

Blood samples for cellular immunity subgroup test: After venous blood is collected by anticoagulant tube, place it in a refrigerator at 2-8°C for storage, record the storage temperature, and send it for testing as soon as possible.

### **11.6.2. Numbering rules of blood samples**

The numbering rules of humoral immunity test blood sample labels are "random number-time point of blood collection-letter of serum submitted for test", for example, "0001-D0-A" means that tube A of the serum sent for testing which was collected by participant No. 0001 for testing the humoral immunogenicity tests before vaccination.

### **11.6.3. Sample detection**

The humoral immunoassay is entrusted to a qualified third party. The specific IgG antibody titer will be detected by ELISA and the neutralizing antibody titer will be

---

detected by live virus neutralization assay. The testing reference material and quality control standards will be provided by the testing laboratory.

The cellular immunoassay is entrusted to a qualified third party. All relevant assays are detected using enzyme-linked immunospot assay (ELISpot). The testing reference material and quality control standards will be provided by the testing laboratory.

### **11.7. Data management**

**Data management plan:** The data administrator writes the data management plan according to the clinical research protocol, and implements it after being reviewed and approved by the sponsor.

**Establishment of the database:** the eCRF is designed by the data administrator according to the clinical research plan, and the EDC is constructed by the database builder. The data administrator writes the data review plan (DVP) according to the plan and eCRF, and the database builder sets up logic verification according to the DVP. Before the EDC system goes online, it conducts a system test (UAT) and writes a test report. The EDC system that has passed the test can only be put into operation after being reviewed and approved by the sponsor.

**Data entry:** Data administrators write data entry guidelines and provide training to researchers and/or EDC entry personnel, who then enter EDCs by researchers and/or EDC entry personnel.

**Authority distribution:** After the EDC system is put into operation, according to the training records and account application status, the system administrator will create accounts and grant different permissions.

---

**Data query:** The data manager writes a data verification plan, which is implemented after approval by the funder. After the data is entered into the EDC, the system will check the data according to the Edit Check built into the data verification plan, and the data with doubts will be automatically sent to the system; the data that cannot be set to be questioned by the system will be sent to manual questions through the EDC, The input personnel or researchers confirm and answer the manual and system queries until the queries are resolved. When the answer fails to resolve the query, the data administrator and clinical monitor can re-query the data point, and all traces are stored in the EDC database.

**External data:** The data administrator writes an external data transmission agreement according to the plan and implementation, and it will take effect after being signed and approved by the sponsor and the designated laboratory of this project. transmission. The data administrator will conduct a consistency check, and the data with problems will be notified to the sponsor by email. After each party modifies the corresponding data or verifies that the data is correct, it will be retransmitted until the relevant data is consistent.

**Medical coding:** The data management unit is responsible for the medical coding of this study. Coded using the version of MedDRA specified in the project DMP.

**Blind review:** After data cleaning, question answering, and database closure (before locking), relevant parties (funders, researchers, data administrators, statisticians) will perform data clarification on the database and biological samples before unblinding. The results are reviewed to form a population classification decision.

**Locking of the database:** After the data is confirmed to be correct through a blind review, the database is locked with written approval, and approved by the co-signature (signature and date) of the unblinding relevant personnel (statistician, researcher, sponsor). The unlocking and re-locking of the database can only be carried out with

---

the written consent of the above-mentioned personnel, and records should be made. After the database is locked, the data manager needs to submit the locked database to the statistician for statistical analysis.

**Data management report:** The data steward writes the data management report after unblinding.

## **11.8. Statistical analysis**

### **11.8.1. Analysis Sets**

#### **➤ Analysis set of efficacy**

**Full analysis set of efficacy(E-FAS):** Include all subjects who followed the intention-to-treat (ITT) principle, entered randomization and completed vaccination, and had at least one case surveillance follow-up after vaccination.

**Modified full analysis set of efficacy(E-mFAS):** It is a subset of E-FAS and includes all subjects who completed vaccination, had negative baseline nucleic acid results, and had at least 1 case surveillance follow-up 14 days after vaccination. Among them, COVID-19 cases with positive nucleic acid or antigen test or confirmed diagnosis within 14 days from enrollment to vaccination will also be excluded from this analysis set.

**Per protocol set of efficacy(E-PPS):** It is a subset of E-mFAS, including all subjects who did not violate the inclusion/exclusion criteria, completed vaccination, had negative baseline nucleic acid results, and had at least one case surveillance follow-up 14 days after vaccination, and did not violate the protocol. Among them, COVID-19 cases with positive nucleic acid or antigen test or confirmed diagnosis within 14 days from enrollment to vaccination will also be excluded from this analysis set.

Cases of E-mFAS and E-PPS are counted from 14 days after vaccination and are

---

mainly used for the evaluation of the main protective efficacy of the vaccine. Among them, E-mFAS is the main analysis set for the evaluation of protective efficacy in this study. E-FAS was used to evaluate the protective efficacy after vaccination.

➤ **Analysis set of immunogenicity**

**Full analysis set of immunogenicity(I-FAS):** Include all subjects in the immunization subgroup who follow the ITT principle, enter randomization and complete vaccination, and have valid antibody data before vaccination.

**Per protocol set of immunogenicity(I-PPS):** Include all subjects in the immunization subgroup who did not violate the inclusion/exclusion criteria, completed the vaccination, had blood samples collected at the evaluation time points, and had valid antibody data. The immunogenicity analysis sets were defined for the immunogenicity evaluation of each group at 7 days, 14 days, and 28 days after vaccination respectively.

**Analysis set of immune persistence(IPS):** Include subjects whose blood samples were collected at all immune persistence evaluation time points and have valid antibody data. The immune persistence analysis set was defined for the immunogenicity evaluation at 3 and 6 months post-vaccination, respectively.

I-FAS and I-PPS were used for immunogenicity analysis. IPS was used for immune persistence analysis.

➤ **Analysis set of safety**

**Safety analysis set(SS):** Include all subjects vaccinated with the study vaccine.

All the above analysis sets will be discussed and decided by the main investigators, funders, statisticians, and data managers in a blinded data review meeting before the database is locked.

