| 5                          | Inclusion and exclusion criteria*                                                                              | X                                               | /  | /   | /   | /   | /    |
| 6                          | Enrollment, assigning randomization number                                                                     | X                                               | /  | /   | /   | /   | /    |
| 7                          | Immunogenicity tests (immunization subgroups only) a                                                | X                                               | X  | X   | X   | X   | X    |
| 8                          | Cellular immunity assays (immunization subgroup only) b                                             | X                                               | X  | X   | X   | X   | /    |
| 9                          | Vaccination                                                                                                    | X                                               | /  | /   | /   | /   | /    |
| 10                         | Observation for 30 minutes after vaccination, train participants to perform safety observations and recordings | X                                               | /  | /   | /   | /   | /    |
| 11                         | Dispensation of diary cards                                                                                    | X                                               | /  | /   | /   | /   | /    |
| 12                         | Distribution of soft measuring tape and thermometers to participants                                           | X                                               | /  | /   | /   | /   | /    |
| 13                         | Review and collect diary card                                                                                  | /                                               | /  | X   | /   | /   | /    |

| On-site Visit # |                                                                | Vaccination until 6 months after
vaccination |    |     |     |     |      |
|----------------------------|----------------------------------------------------------------|-------------------------------------------------|----|-----|-----|-----|------|

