## **6.2. Study endpoint(s)**

### **6.2.1. Primary endpoint(s)**

➤ The primary endpoint(s) of protective efficacy

1)The person-year incidence rate of symptomatic COVID-19 cases of any severity (Appendix 1) occurring from 14 days after booster vaccination of the investigational

---

vaccine or placebo in adults aged 18 and older who have completed 2 or 3 doses of inactivated COVID-19 vaccines.

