## **6.9. Follow-up plan**

Within 28 days after the booster vaccination, all participants need to conduct at least 3 on-site visits to complete enrollment (visit 1), vaccination (visit 1), distribution, and collection of diary cards and contact cards (visit 1, visit 3, visit 4). The participants in the immunogenicity subgroup also need to collect blood for immunogenicity (visit 1-6).

From the 7th day to the 180th day after the booster vaccination, all participants

---

need to conduct remote visits at least 22 times (about 8 times per month from the 7th day to the 90th day after the vaccination; about once per month from the 90th day to the 180th day after the vaccination), to carry out routine monitoring of VE and/or case monitoring after booster vaccination. At the same time, AEs, SAEs, AESIs, and pregnancy events (including pregnancy outcomes, delivery characteristics, the condition of the newborn, and the growth and development within 1 month after birth) need to be collected.

In addition to the on-site visits and remote visits mentioned above, the investigators may increase the on-site visits or remote visits to the participants to an appropriate frequency according to actual needs, and make follow-up records.

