#### **11.4. Safety observation method**

##### **11.4.1. Safety observation time and method**

###### **(1) Within 28 days after vaccination**

Participants will be observed at the vaccination site for 30 minutes after vaccination. Investigators who have been trained and authorized need to systematically observe and measure the body temperature of each participant 30 minutes after vaccination, and record all AEs within 30 minutes after vaccination in detail. AEs will be observed and recorded through the Diary Card from 0 to 14 days after vaccination, and AEs will be collected and recorded through the Contact Card from 15 to 28 days after vaccination.

Investigators should check the original safety information of the Diary Card and Contact Card in time and input it into EDC after checking. Investigators should verify the name, duration, and severity of any AE and evaluate and determine its relationship to vaccination. Measures taken in response to the AE, combined treatment, and outcome of the AE, whether the event was a serious adverse event, and whether the event led to study discontinuation, must also be documented.

---

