#### **11.8.2.3. Protection effectiveness analysis**

The person-year incidence rates and 95% confidence interval(CI) of COVID-19 confirmed by the central laboratory with clinical symptoms will be calculated among the test group and the control group 14 days after the vaccination, and the Poisson regression model will be used to analyze the statistical differences between the groups. VE and 95% CI based on the person-year incidence rates will be estimated with the model. The Poisson regression model takes the number of patients as the dependent variable, grouping as the fixed effect, and the exposure person-years of the participants as the offset, using the log connection function.

Person-year incidence rate=(number of cases)/(exposure person-years of the participants)×100%. In the calculation of the exposure person-years, the starting time is the 14th day after the vaccination, and the ending time is the day when a COVID-19 case was first confirmed. If the RT-PCR or antigen test was positive but not confirmed as a COVID-19 case, the person-year incidence rate was calculated using the RT-PCR or antigen test date as the termination time. VE rate=1- (person-year incidence rate of the test group)/(person-year incidence rate of the control group).

---

The VE will be evaluated in the prevention of clinically symptomatic COVID-19 confirmed by central laboratory virology 14 days after vaccination based on the sets of E-mFAS and E-PPS. The evaluation of VE based on E-mFAS is the main analysis result of this study.

In addition, the VE of the vaccine against clinically symptomatic COVID-19 confirmed by central laboratory virology 7 days after vaccination will be evaluated based on E-mFAS, and the statistical method is the same as the primary efficacy endpoint.

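### The early-infection exclusion for E-mFAS and E-PPS is worded so that it covers no day after vaccination, and its evident meaning blurs day 14 and empties the 7-day efficacy analysis of its early cases

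*Protocol*

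**What the plan says.** Protocol section 11.8.1 defines E-mFAS and names it the main set for protective efficacy. E-PPS is a subset of it. Both definitions carry the same exclusion: COVID-19 cases with a positive nucleic acid or antigen test, or "confirmed diagnosis within 14 days from enrollment to vaccination will also be excluded from this analysis set". The next paragraph states that "Cases of E-mFAS and E-PPS are counted from 14 days after vaccination".

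Other sections fix the dates on which this rule depends:

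- Section 6.9 has participants attend on site "to complete enrollment (visit 1), vaccination (visit 1"). Table 1 places "Enrollment, assigning randomization number" in the Visit 1, D0 column, as it does vaccination, and section 9.3 gives the dose on Day 0.
- Section 6.2.1 takes primary cases "occurring from 14 days after booster vaccination of the investigational" vaccine or placebo.
- Section 11.8.2.3: "In the calculation of the exposure person-years, the starting time is the 14"th day after vaccination. Exposure ends at the first confirmed case or, for a positive test that is not confirmed as a case, on the test date.
- Section 11.8.2.3 also evaluates efficacy from 7 days after vaccination and names E-mFAS as the set.
- Section 11.4.1, on safety: "AEs will be observed and recorded through the Diary Card from 0 to 14 days after vaccination", with the Contact Card covering days 15 to 28.

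**The concern.** The exclusion should mirror the case window: whoever is already infected when counting opens on day 14 should be out. The sentence instead bounds the interval by two events on the same day. What is left is Day 0, and E-mFAS already requires a negative baseline nucleic acid result.

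A reader will repair the sentence to mean up to 14 days after vaccination. That repair raises two further problems. The excluded interval may then share day 14 with the case window, and the exclusion removes the cases that the 7-day analysis exists to count. At stake is whether membership of the primary set can be derived from the protocol alone, and whether the 7-day analysis can be run as described.

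**Working it through.** **1. Literal reading.** Enrolment is Day 0 and vaccination is Day 0, so the interval between them contains no day from 1 to 13. Take a participant first positive on day 5, as an example. The exclusion does not apply. By section 11.8.2.3 exposure starts on day 14 and ends on day 5: 5 − 14 = −9 days. The Poisson model uses exposure as the offset with a log link, which needs positive exposure. The set definition and the exposure rule do not fit together.

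**2. Intended reading (to 14 days after vaccination).**

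| First positive | Exclusion, day 14 included | Exclusion, day 14 not included | Case and exposure window |
|---|---|---|---|
| Day 13 | excluded | excluded | not open |
| Day 14 | excluded | kept | open |
| Day 15 | kept | kept | open |

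Day 14 is in conflict only if the 14-day limit is inclusive. That is the ordinary sense and matches the safety windows (0–14, then 15–28), but no section defines it for efficacy. The synopsis defines how many days apart two dates are, which is a different phrase and does not settle the matter.

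**3. The plan's own figures.** Inputs from section 6.5.1: VE 60%, margin 30%, 1:1 allocation, one-sided 0.025, power 90%, incidence 9%. Conditional on T cases, the vaccine-arm count is binomial with

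- p0 = 0.7/1.7 = 0.4118 at the margin
- p1 = 0.4/1.4 = 0.2857 at the expected VE

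At T = 162 the critical value is 54, exact alpha is 0.0247 and power is 92.2%. Exact power first reaches 90% at T = 154 and stays at or above it from T = 160, so 162 is consistent with the stated method. Participants per arm: 162/(0.09 × 1.4) = 1,285.7, that is 1,286 as stated. With 20% non-evaluable: 1,286/0.8 = 1,607.5, rounded up to 1,608, against 1,600 planned. None of these figures depends on the exclusion wording.

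**4. Size of the day-14 overlap.** Assume that the 162 cases are spread evenly over follow-up.

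- Days 14–180 (167 days): 162/167 = 0.97 cases on day 14, or 0.6%.
- Days 14–90 (77 days): 162/77 = 2.1 cases on day 14, or 1.3%.

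Exact power without these cases:

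| Cases | Critical value | Exact power |
|---|---|---|
| 162 | 54 | 92.2% |
| 161 | 53 | 90.3% |
| 160 | 53 | 91.2% |

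**5. The 7-day analysis.** Its distinctive content is the cases on days 7–13. On the intended reading, everyone with a positive test or diagnosis on those days has been removed from E-mFAS. Exposure counted from day 7 would then include seven days that are free of cases by construction, and the result would largely repeat the 14-day one. The literal reading keeps those cases but brings back the problem in step 1. Neither reading serves both analyses.

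**The case against.** The strongest reply is that this is a drafting or translation slip that no analyst would apply literally. Day 14 appears in the endpoint, the counting rule and the exposure rule, so the sentence can be read as a clean partition: before day 14 out, from day 14 in. The safety diary windows do not govern efficacy, and day conventions are often settled in the SAP. Much of this stands. The intent is clear, and the day-14 overlap is an available reading that the text does not force. However, the protocol itself states the primary set wrongly, in two definitions, and an SAP that corrected it would depart from the protocol. The partition reading also leaves the 7-day conflict in place.

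Three stronger inferences are tempting, and the documents do not support them.

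- A reader might infer that participants infected early would stay in the set and distort the primary estimate, through recently immune person-time or a later positive counted as a primary case. Section 11.8.2.3 ends exposure at first confirmation or positive test, so an infection detected before day 14 has no valid exposure and adds little. Routine monitoring under section 6.6 starts on day 7, so some earlier infections would go undetected under either wording.
- A reader might infer that the boundary could be chosen once results are known. Sections 11.7 and 11.8.1 place the classification in a blinded review before database lock, so it cannot be chosen to favour an arm.
- A reader might infer that one day-14 case could decide the trial, because 54 of 162 is a sharp threshold. That threshold belongs to the sample-size method. The planned primary analysis is Poisson regression, and at VE 60% about 162 × 0.2857 = 46 vaccine-arm cases are expected.

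**Conclusion.** Wrong as written. The exclusion in both efficacy sets covers no day after vaccination and so does not do what the day-14 case window requires. Read literally, it produces exposure that ends before it starts. Read as intended, it leaves day 14 open to two classifications and takes the day 7–13 cases out of the set named for the 7-day analysis.

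The numerical effect on the primary result is small: about 1 to 2 of 162 cases (0.6% to 1.3%), with exact power between 90.3% and 92.2% and the figures of 162, 1,286 and 1,600 unchanged. This rests on an even spread of cases over days 14–180 or 14–90 and on an inclusive 14-day limit. A wave of infection falling on day 14 for many participants would raise the count. The conflict with the 7-day analysis needs no numerical assumption: on the intended reading that analysis loses all its day 7–13 cases.

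**What to change.** In section 11.8.1, replace the exclusion in both E-mFAS and E-PPS with: participants with a positive nucleic acid or antigen test, or a confirmed COVID-19 diagnosis, from day 0 through day 13 after vaccination are excluded. Keep case counting and exposure from day 14 inclusive, so that each day belongs to exactly one window.

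In section 11.8.2.3, move the 7-day analysis to a matching set that excludes only positives and diagnoses from day 0 through day 6, with cases and exposure counted from day 7. The follow-up condition for that set should be tied to day 7 in the same way.

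The cost is wording in two definitions and one added set for an exploratory analysis. It needs no new data, no change to visits and no change to the sample size.
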